### Design

A mixed methods multicentre study to establish the feasibility of a RCT of feeding methods in patients with stages III and IV head and neck cancer receiving CRT with curative intent. The work will be conducted over 24 months.

The components are:A multicentre randomised controlled pilot feasibility trial comparing oral feeding plus pre-treatment gastrostomy versus oral feeding plus as required nasogastric tube feeding in patients with HNSCC. Patients will be randomised on a 1:1 basis and stratified by IMRT and by the treating centre.A qualitative process evaluation to inform the trial design by investigating patient, carer and staff experiences of trial participation.A modelling exercise to synthesise available evidence and provide preliminary estimates of cost-effectiveness and value of information from future research.

### Setting

The setting was five tertiary NHS centres for HNSCC. For our definitive trial, additional centres will be recruited via our links with the National Cancer Research Network, Comprehensive Clinical Research Network and from respondents to our national survey [16].

#### Ethical considerations

Ethical approval was sought and granted by the Newcastle and North Tyneside 2 Committee, NHS Health Research Authority, reference 14/NE/0045.

### Target population

The target population will be patients with stage III and IV HNSCC who receive primary CRT with curative intent.

Inclusion criteria:

(1) Grade 1 pre-treatment dysphagia, as defined by Common Terminology Criteria for Adverse Events v4.0 (defined as asymptomatic/symptomatic/able to eat regular diet). (2) Consent to be randomised.

Exclusion criteria:

Patients who (1) decline to participate, (2) are unable to give informed consent, (3) cannot receive a gastrostomy for medical reasons, (4) do not receive treatment with curative intent and (5) patients with malnutrition requiring immediate initiation of enteral feeding.

Clinical experience suggests that patients with primary sites in the oropharynx, larynx, nasopharynx and unknown primaries are those who will fulfil the inclusion criteria (~35 to 40 % of all HNSCC patients).

### Interventions

Pre-CRT gastrostomy arm: endoscopic or radiologic gastrostomy will be placed before commencement of CRT. Given the pragmatic nature of this study and equivalent success rates with either technique, the choice of method of insertion will be left to local protocols of the treating centre. Patients will continue with oral feeding and commence use liquid nutrition through the G tube when they are unable to maintain an adequate oral intake to meet their nutritional requirements (<75 % of requirements based on a dietetic assessment of 24-h recall by patients).

No pre-CRT gastrostomy arm: this group will continue with oral feeding or have a nasogastric tube if required during treatment. The decision to place a nasogastric tube will be based on clinical assessment, patient request and published guidelines [6], patient request for gastrostomy tube may also lead to gastrostomy placement. Based on published prospective data, we anticipate that <10 % will convert from NG tube to G tube during the study.

### Outcomes measures

The primary outcome of feasibility will comprise of the following entities:Willingness of patients to be randomised (assessed via review of patient screening logs) defined as:i.The number of patients consenting to be randomised as a proportion of all patients approached about the trial, with reasons for non-consentii.Qualitative assessment of barriers and facilitators to recruitment
Willingness of clinicians to randomise patients—assessed via qualitative interviewsAssessment of retention and drop-out rates, defined as:i.The number of patients who start randomised treatment as a proportion of the number randomised, with reasons for early drop outsii.The number of patients who complete randomised treatment as a proportion of the number randomised, with reasons for drop outs (including death)iii.Completeness of MD Anderson Dysphagia Inventory (MDADI) assessment within 6 monthsiv.Qualitative assessment of barriers and facilitators to data collection and participant retention

Secondary outcome measures are:

The following scores/ measures will be requested at baseline (before treatment) and at 3 and 6 months after treatment (5 and 8 months from randomisation):A.The MDADI is a self-administered questionnaire designed specifically for evaluating the impact of dysphagia on the quality of life of patients with head and neck cancers [30]. This will be our primary outcome measure in the full trial.B.Quality-of-life outcomes

We will use two questionnaires to assess quality of life outcomes. The European Organization for Research and Treatment of Cancer questionnaire EORTC QLQ-C30 (version 3.0) is a cancer-specific instrument, has a multidimensional structure, appropriate for self-administration and is applicable across a range of cultural settings [31]. The EORTC QLQ - H&N35 is the head and neck module for EORTC QLQ-C30 (version 3.0) and is intended for use in conjunction with the QLQ-C30 in patients with head and neck cancer [32].C.Short form 36

The SF-36 is a multi-purpose, short-form health survey with 36 questions. It yields an eight-scale profile of functional health and well-being scores as well as psychometrically based physical and mental health summary measures and a preference-based health utility index that will be used to derive quality-adjusted life-years for a cost-utility analysis conducted as part of a subsequent full trial.D.Use of health and personal social services and costs to patients and their families/carers

For the definitive economic evaluation costs to patients and their families/carers, the NHS and personal social services will be elicited. Within the feasibility study, we will develop the tools necessary to elicit these costs. Specifically, we will develop case report forms and questionnaires to capture use of services and patient/family/carer costs. The content of these forms will be developed in consultation with the study team, our existing item bank of questions, web based resources e.g. www.dirum.org and experience from other RCTs of nutritional interventions e.g. the recent SIGNET trial [33]. The tool developed will be administered at 3 and 6 months after treatment.E.Nutritional parameters

We will measure the body mass index before treatment, at 3 months and at 6 months following treatment. We will also measure weekly weight changes during treatment and the quantity of enteral nutrition consumed.F.Oral health monitoring

We will perform oral health assessment before commencing treatment and the end of 6 months for all dentate patients. A full dental chart with panaromic radiographs will be performed at pre-treatment and at 6 months. Periodontal and oral hygiene assessment and plaque scores will also form part of this assessment and be documented.

### Statistical considerations

Target recruitment is 60 patients (30 per arm of the study) [34]. As a feasibility study, we will provide an assessment of recruitment and compliance rates to inform future trial design. Statistical analyses are according to a confidence interval rather than a hypothesis testing approach. Analyses will be descriptive reporting rates as proportions with confidence intervals and graphical analyses of longitudinal data. Recruitment is dependent on the number of patients approached but should be no lower than 50 %. The upper limit of the 95 % confidence interval for the proportion of patients recruited should exceed 50 %. If 120 patients were approached and 50 % were recruited (60 patients randomised), the 95 % confidence interval for the recruitment rate would have width ±9 %. This would provide a good level of accuracy to assess the acceptability of the recruitment rate.

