### Progression criteria to phase III trial

The decision to move to a phase III trial will be based on:Adequate timely recruitment with a 50 % recruitment rate.Completeness of outcome measurement (MDADI at 6 months): excluding those individuals who die during the study period. This outcome data successfully collected should be greater than or equal to 80 %, as this will be the primary outcome for the planned phase III trial.Economic criteria of EVOI to suggest further research likely to be worthwhile.

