##### Patient recruitment phase

We will focus on patients’ and professionals’ experiences of recruitment. Patients will be recruited from multidisciplinary clinics, with trial information being provided by research nurses. We will conduct qualitative interviews with patients who have consented to take part in the trial (*n* = 5 in the G-tube group; *n* = 5 in oral feeding group) and where possible, those that decline to take part either at recruitment or who withdraw at the point of randomisation (*n* = 10). We will focus on their experiences and understandings of trial processes (e.g. the information they were given; the recruitment encounter; their ideas and/or concerns about randomisation and consent) and the intervention (willingness to undergo either feeding option; ideas and/or concerns about impact on health and acceptability).

Ideally, we would interview patients within 2 weeks of recruitment discussions. Patients will be offered a choice of location and method (telephone; face-to-face) of interview. We know that individuals often discuss clinical decisions with other people [36] so patients who wish to involve a family member in their interview will be able to do so.

We will also conduct further interviews with professionals involved in some aspect of patient recruitment (*n* = 3–5 per site) and, where possible, observe multidisciplinary team meetings to understand the process of identification of eligible patients (*n* = 1–3 per site). Again, where possible, study recruitment discussions (either at treatment planning clinic or subsequent discussion with clinical nurse specialist) will, with consent, be observed (*n* = 3–6 per site). An initial visit to each site will take place shortly after (1–2 months) the site commences patient recruitment. The timing of subsequent visits to a site will be driven by factors such as variation in recruitment rates between sites or changes in key personnel.

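### The recruitment criterion appears as a 50 % floor and as an upper confidence limit above 50 %; the plan does not say which governs, and they give different decisions for observed rates of about 42 % to just under 50 %

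*Protocol article*

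**What the plan says.** Three statements in the protocol article bear on the recruitment criterion.

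- Statistical considerations, the floor: "Recruitment is dependent on the number of patients approached but should be no lower than 50" %.
- Statistical considerations, the next sentence: the upper limit of the 95 % "confidence interval for the proportion of patients recruited should exceed 50" %.
- Progression criteria to phase III trial: "Adequate timely recruitment with a 50" % recruitment rate. No confidence limit is mentioned, and nothing says whether the 50 % is an observed value.

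The rate is defined under Outcomes measures as "The number of patients consenting to be randomised as a proportion of all patients approached about the trial". The planned size is given as "Target recruitment is 60 patients (30 per arm of the study"). Precision is illustrated with a conditional example that begins "If 120 patients were approached and 50" % were recruited; the 95 % "confidence interval for the recruitment rate would have width" ±9 %. The article sets no number approached beyond this example.

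**The concern.** The floor and the confidence-limit condition stand in adjacent sentences, and nothing says how they combine. An observed rate of 50 % or more always has an upper limit above 50 %. If both must hold, the second sentence does no work. If the second sentence is the operative rule, it admits rates that the first excludes. It asks only that 50 % cannot be ruled out, which is easier to satisfy when the estimate is less precise.

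Recruitment is the first component of the primary feasibility outcome and the first progression criterion. The Background says that this feasibility study is being done because a similar Australian trial could not recruit enough patients. If the recruitment result falls between the two thresholds, the decision on this criterion depends on which sentence is applied after the result is known.

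**Working it through.** **Inputs.** From Statistical considerations: target 60 randomised, example of 120 approached, floor 50 %, 95 % interval, stated half-width ±9 %. From Outcomes measures: the rate is consenting patients divided by patients approached. The true rates of 40 %, 45 % and 50 %, and numbers approached other than 120 (apart from those that follow from the target of 60), are assumptions chosen to show a range.

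**1. The plan's own figure.** Half-width = 1.96 × √(p(1 − p)/n). With p = 0.5 and n = 120 this is 1.96 × √(0.25/120) = 0.0895, or 8.95 points. The stated ±9 % reproduces.

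**2. Where each rule starts to pass at 120 approached.**

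- Floor: 60/120 = 50 %.
- Upper limit: p + 1.96 × √(p(1 − p)/120) > 0.5.
  - 50/120: 0.4167 + 1.96 × √(0.4167 × 0.5833/120) = 0.4167 + 0.0882 = 0.505, so it passes (interval 32.8 % to 50.5 %).
  - 49/120: 0.4083 + 0.0879 = 0.496, so it fails.
  - The Wilson interval also gives 50. The exact interval gives 49 (40.8 %).

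Results of 50 to 59 out of 120 (41.7 % to 49.2 %) therefore pass the limit rule and fail the floor.

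**3. With the target of 60 met.** A rate below 50 % then means more than 120 approached. At 60/143 the rate is 42.0 % and the upper limit is 0.4196 + 0.0809 = 0.5005, which passes. At 60/144 it is 0.4167 + 0.0805 = 0.497, which fails (the exact interval still passes at 144). The rules disagree from 60/121 (49.6 %) to 60/143 (42.0 %).

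**4. Chance of passing at 120 approached** (exact binomial tail; P(X ≥ 50) for the limit rule, P(X ≥ 60) for the floor):

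| True rate | Upper-limit rule | Floor | Difference: passes the limit rule only |
|---|---|---|---|
| 40 % | 38.8 % | 1.7 % | 37.1 % |
| 45 % | 79.5 % | 15.6 % | 63.9 % |
| 50 % | 97.3 % | 53.6 % | 43.7 % |

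**5. Dependence on the number approached.** The lowest passing rate under the limit rule (simple interval, as in the plan's figure) is 87/200 = 43.5 %, 50/120 = 41.7 %, 41/100 = 41.0 %, 32/80 = 40.0 % and 23/60 = 38.3 %. At a true rate of 40 % the chance of passing is 17 % with 200 approached, 39 % with 120 and 65 % with 60. The floor is 50 % throughout.

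**The case against.** The best defence is that the decision is set out in the progression section, which names a 50 % rate and no confidence limit. The natural reading is the observed rate, and the statistical section would then only describe how that rate is reported. This reading is plausible, but the article does not state it. The confidence-limit sentence is worded as a requirement, and the same section says that analyses follow a confidence-interval approach, so a reader could equally take the limit as the test.

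Other parts of the defence stand:

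- **The conditions do not exclude each other.** A reader might call them incompatible. They are nested, and both hold for any observed rate of 50 % or more. The fault is that they are unreconciled.
- **The small-number effect is bounded.** With fewer than 120 approached, a rate below 50 % means fewer than 60 recruited. Such a trial also misses its target and could hardly count as adequate, timely recruitment. This applies to 50 to 59 out of 120 as well. It does not apply to step 3, where the target is met and the rules still disagree. A reader might press the point to very small numbers approached, but those cases fall so far short of the target that they add nothing.
- **The ±9 % is correct.** A reader might argue that clustering by centre makes it too narrow. The article gives no intra-centre correlation. It mentions "variation in recruitment rates between sites" only as an example of what may drive the timing of qualitative site visits. That does not support a numerical criticism of the interval.
- **Recruitment is not the only criterion.** Outcome completeness and value of information are assessed as well, so a pass on recruitment alone does not start a phase III trial.

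**Conclusion.** The point holds as an unreconciled decision threshold. At 120 approached, the two printed conditions disagree for every result from 50 to 59 recruited. With 60 recruited they disagree from 121 to 143 approached. If the confidence-limit sentence is used as the go rule, a true rate of 45 % passes about five times as often as under the floor (79.5 % against 15.6 %), and a true rate of 40 % passes in 38.8 % of trials against 1.7 %.

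These probabilities assume independent patients, 120 approached and the simple or Wilson interval. With the exact interval the limit rule passes from 49/120, and the probabilities rise to 46.0 % at a true 40 % and 84.4 % at a true 45 %.

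A reader might conclude that the plan adopts the weaker rule. The documents do not show that; they leave the choice open. This is more than detail left to a fuller document, because the article prints both thresholds.

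**What to change.** State one rule, in the same words, in Statistical considerations and in Progression criteria to phase III trial. Use the Outcomes measures definition of the rate (patients consenting to be randomised out of all approached).

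- **Go:** observed rate at least 50 %, reported with its 95 % confidence interval.
- **Amend recruitment and review:** observed rate below 50 % but upper 95 % limit above 50 %. This keeps what the limit can show, that 50 % is not excluded, without treating it as a pass.
- Apply the rule once, at the end of recruitment, alongside the target of 60 randomised. Do not require a fixed 120 approached: at 60 % uptake the target is reached with 100 approached (60/0.60), and such a minimum would block the rule in a successful trial.
- Name the interval method, since the boundary moves by one patient between methods at 120 approached.

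The ±9 % statement can stay.

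The cost is wording only. The article reports that recruitment was already under way, so the rule should be settled before the final rate is examined. The downside is strictness: with 120 approached and a true rate of exactly 50 %, an outright go occurs 53.6 % of the time. The amend zone takes a further 43.7 %, which leaves 2.7 % below both thresholds.

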### Progression criteria to phase III trial

The decision to move to a phase III trial will be based on:Adequate timely recruitment with a 50 % recruitment rate.Completeness of outcome measurement (MDADI at 6 months): excluding those individuals who die during the study period. This outcome data successfully collected should be greater than or equal to 80 %, as this will be the primary outcome for the planned phase III trial.Economic criteria of EVOI to suggest further research likely to be worthwhile.

#### Qualitative process evaluation

The integrated qualitative process evaluation will explore barriers and facilitators to trial implementation. Through regular feedback of emerging findings to the trial team it will inform the day-to-day running of the pilot trial and optimise recruitment and retention. It will also identify aspects of trial processes which could be improved for the definitive trial.A.Normalisation process theory

Our analysis of facilitators and barriers to trial participation will be informed by normalisation process theory [35]. Normalisation process theory considers factors that affect implementation in relation to four key areas; how people make sense of a new practice (in this case—the trial) (coherence); the willingness of people to sign-up and commit to the new practice (cognitive participation); their ability to take on the work required of the practice (collective action); and activity undertaken to monitor and review the practice (reflexive monitoring). This theory is increasingly being used in studies of the implementation of interventions in health care (www.normalizationprocess.org). In the current study, we will consider how well trial processes are introduced and incorporated at each site for both patient and professional groups.B.Methods and sampling

Numbers have been included to give an indication of the amount of data to be collected. We have given particular thought, for example, to whether there might be significant subgroups of patients or professionals, which would require an additional layer of data collection and analysis. However, in keeping with the principles of rigorous qualitative research, the actual sample size will be informed by the point of data saturation; we will be responsive to the study context and anticipate that in some cases, fewer interviews or observations will be conducted, and in others, additional data will be collected in response to our emerging analysis or study events. We aim to achieve a balance between spread of data (to avoid missing key events or issues) and depth (a manageable data set that allows for in-depth analysis); having the flexibility to identify and focus in on those issues which our analysis suggests is key to successful study implementation.

##### Data collection will focus on three inter-related phases over the duration of the trial

Following appropriate consent, we will include interviews with health professionals (*n* = 15–24); patients (*n* = 32–36); observation of recruitment discussions (*n* = 9–18); and observations of multidisciplinary team meetings (*n* = 6–15); details below.

##### Pre-implementation of TUBE pilot trial

In order to understand the context, professionals’ views and expectations and to map patient pathways, we will visit each study site. We will conduct formal interviews with key individuals (*n* = 2–3 per site) involved in treatment planning for HNSCC (e.g. nurses; speech therapists; ENT surgeons).

##### Patient recruitment phase

We will focus on patients’ and professionals’ experiences of recruitment. Patients will be recruited from multidisciplinary clinics, with trial information being provided by research nurses. We will conduct qualitative interviews with patients who have consented to take part in the trial (*n* = 5 in the G-tube group; *n* = 5 in oral feeding group) and where possible, those that decline to take part either at recruitment or who withdraw at the point of randomisation (*n* = 10). We will focus on their experiences and understandings of trial processes (e.g. the information they were given; the recruitment encounter; their ideas and/or concerns about randomisation and consent) and the intervention (willingness to undergo either feeding option; ideas and/or concerns about impact on health and acceptability).

Ideally, we would interview patients within 2 weeks of recruitment discussions. Patients will be offered a choice of location and method (telephone; face-to-face) of interview. We know that individuals often discuss clinical decisions with other people [36] so patients who wish to involve a family member in their interview will be able to do so.

We will also conduct further interviews with professionals involved in some aspect of patient recruitment (*n* = 3–5 per site) and, where possible, observe multidisciplinary team meetings to understand the process of identification of eligible patients (*n* = 1–3 per site). Again, where possible, study recruitment discussions (either at treatment planning clinic or subsequent discussion with clinical nurse specialist) will, with consent, be observed (*n* = 3–6 per site). An initial visit to each site will take place shortly after (1–2 months) the site commences patient recruitment. The timing of subsequent visits to a site will be driven by factors such as variation in recruitment rates between sites or changes in key personnel.

